## Abstract

**Introduction:**

Vital signs such as heart rate (HR) and respiratory rate (RR), crucial for clinical assessment, are often challenging to measure in paediatric populations. Remote photoplethysmography (rPPG), a video-based measurement tool, has demonstrated accuracy in adults. The objective of this study is to compare HR and RR measurements obtained using rPPG with those from standard clinical monitoring in a paediatric population.

**Methods and analysis:**

This is a monocentric, prospective study enrolling 600 paediatric participants. Each participant will have standard monitoring electrodes (ECG/impedance) placed on the chest while seated facing a camera for rPPG recording. Simultaneous HR and RR measurements will be recorded over periods of 30 and 60 s using both the standard monitor and the rPPG device. The intraclass correlation coefficient will be calculated to assess agreement between the rPPG and standard monitor measurements.

**Ethics and dissemination:**

The study protocol has been approved by the French Agency for the Safety of Health Products (ANSM (Agence nationale de sécurité du médicament) registration no. IDRCB 2023-A02524-41) and by a French ethics committee (CPP Sud Méditerranée III at 29 August 2024, n°2024-A01324-43). The study’s findings will be published in peer-reviewed journals and disseminated at national and international conferences and through press releases.

**Trial registration number:**

Clinical Trials Registry (NCT06231654).

STRENGTHS AND LIMITATIONS OF THIS STUDYThis study evaluates the application of a remote photoplethysmography (rPPG) imaging system in a real-world clinical setting.A diverse patient population, encompassing various age groups, genders and skin phototypes, is included.A standard acquisition system is employed as a control measure.A limitation of rPPG is the requirement for minimal patient movement during measurement, a challenge particularly in children.

## Introduction

 In paediatric clinical evaluation, the inherent vulnerability of children compels clinicians to assess their clinical condition quickly and efficiently. Initial measurement of vital signs allows the clinician to promptly determine whether a patient is stable. Particularly, heart rate (HR), respiratory rate (RR), oxygen saturation and blood pressure serve as objective indicators of the child’s circulatory and respiratory status.^1^ In clinical practice, manual measurements have become obsolete. Commonly used methods for measuring vital signs—such as using ECG electrodes or pulse oximetry sensors for HR and thoracic straps or chest electrodes for RR—can present practical challenges.^2^ In emergency settings, accurately measuring these vital signs requires specialised equipment, adequate staffing and sufficient time—all of which are often limited due to high patient volumes. Moreover, these measurements often occur under suboptimal conditions, such as when children are agitated or in pain. This can lead to unreliable readings precisely when accuracy is essential for assessing clinical severity. Photoplethysmography detects variations in blood volume within microvascular tissue beneath the skin’s surface. Each heartbeat induces changes in arterial and arteriolar blood volume, measurable optically.^3 4^ Conventionally, this technique uses a LED sensor placed on a finger, ear or forehead.

For adult populations, innovative methods of vital sign measurement have emerged, demonstrating acceptable reliability and accuracy compared with conventional reference techniques. Among these is remote photoplethysmography (rPPG), a method allowing rapid assessment of vital signs through a simple facial recording captured by a camera. rPPG is an innovative, non-invasive optical approach that measures pulse waves generated by cardiac activity through peripheral blood perfusion. This technology offers significant advantages: ease of use, low cost, safety, convenience and the capacity to measure multiple physiological parameters simultaneously. The company I-Virtual has significantly contributed to advancing rPPG technology, which relies on analysing variations in the facial skin’s colour spectrum to extract photoplethysmographic signals corresponding to vital signs.^5^ Their web application, Caducy, using rPPG technology, can be accessed on various devices and browsers. The operation of the rPPG method through this application is straightforward and rapid: the user places the camera (of a smartphone, tablet or computer) at an appropriate distance to capture a selfie (ensuring the entire face is visible on the screen). The application then analyses and provides vital sign parameters within 30 to 60 s.^6^ On 25 January 2023, I-Virtual’s Caducy received CE Class IIa certification as a medical device for vital sign measurement via webcam, making it the first company worldwide to obtain CE marking for this specific type of technology.^7 8^ However, the use of rPPG technology has not yet been investigated in paediatric patients. Given its ease of use, rapidity, minimal equipment needs, absence of physical contact and existing certification for adult use, rPPG (via Caducy) could potentially address the challenges of measuring vital signs in paediatric settings.

## Method

### Study aim

The aim of the study is to evaluate the feasibility and accuracy of using rPPG technology through the Caducy application in paediatric patients.

### Study design

This is a prospective, interventional, monocentric study conducted at Lenval University Children’s Hospital, Nice (France (FR)). We plan to enrol 600 paediatric patients admitted to the paediatric emergency department (PED).

#### Eligibility criteria

Eligibility and exclusion criteria are listed in table 1.

**Table 1 T1:** List of eligibility and exclusion criteria

Eligibility criteria	Exclusion criteria
Age 3 to 17 years Admitted to the PED Signed consent by one of the two parents or the holder of parental authority Affiliation to a national social security scheme	Presence of vital distress Absence or withdrawal of parental consent Patients with neurocognitive conditions Medical history of cardiac arrhythmia, pathological tremors, muscle spasms, scleroderma Patients whose parents or legal guardians do not understand and/or speak French

PED, paediatric emergency department.

### Study procedure

Patients participating in the study will be recruited from our PED. Every patient presenting to PED will be triaged by the admitting nurse. During the study period, any admission meeting the inclusion and exclusion criteria will be eligible for enrolment in our protocol during the day, depending on the availability of the clinical study technician. On arrival, an initial clinical assessment will be performed. A clinical study technician will then explain the objective and procedures of the study to the parents and to the child if they are of sufficient age and maturity to understand. After obtaining informed consent and registering the child, participants will be seated with their parents in a quiet office, where lighting conditions will be optimised to ensure accurate functioning of the Caducy application. The following data will then be collected: sex, age and phototype according to Fitzpatrick’s classification ranging from phototype 1 to 6.^9^ The child will be seated on a chair facing a camera connected to a laptop running the Caducy Medical Device software. Simultaneously and according to standard clinical procedure, three thoracic ECG electrodes will be placed on the patient, used to measure both HR and RR. The first two electrodes will be positioned on the mid-clavicular lines at the level of the second intercostal spaces, while the third electrode will be placed subcostally on the left side. The electrodes will then be connected to a Mindray ePM10 monitor. Once the child is calm and correctly positioned, the Caducy application will be initiated. Simultaneously, the Mindray monitor will record vital signs. To facilitate patient cooperation, hypnotic visual stimuli—such as kaleidoscope-type videos—will be displayed during image capture; these videos will have a dark tone to specifically reduce interference from ambient lighting. After 30 and 60 s, the HR and RR values obtained from the Caducy application (using the rPPG method) will be collected. Concurrently, HR and RR values from the Mindray monitor will also be recorded for comparison and clinical purposes (figure 1). The total duration of each patient’s participation is estimated at approximately 20 min, including preparation and data collection.

**Figure 1 F1:**
[figure not shown]
HR and RR measurements using Mindray monitor and Caducy app. The illustration used in this article was generated by an AI-based tool (OpenAI’s ChatGPT) at the explicit request of the authors. This image was created specifically for this work and is free from third-party copyright restrictions. The authors retain unrestricted rights to reproduce, distribute and display this image for academic, clinical and educational purposes. HR, heart rate; NBP, non-invasive blood pressure; RR, respiratory rate.

### Medical device

The reference device consists of an approved and validated Mindray ePM10 monitor.^10^

HR will be measured using an ECG system (unit: beats per minute).RR will be measured using thoracic electrodes (unit: respirations per minute).

The Caducy Medical Device Software is the system used for the rPPG measurements. This software operates using an algorithm developed by I-Virtual.^11^

The measurement process consists of four successive steps:

Step 1: Determination of the region of interest (ROI). This step involves identifying the facial skin area for HR analysis and delineating the upper chest region for RR assessment.Step 2: The facial ROI images are analysed to measure the red, green and blue colour channels.Step 3: The algorithm tracks the variations in these colour channels and the movements of the upper chest, over a defined time interval, to determine respectively the physiological parameters, HR and RR.Step 4: The calculated HR and RR values are consolidated into a structured digital record, each assigned a unique identifier. This record is then securely stored in a centralised health database hosting, ensuring data integrity, traceability and compliance with data protection standards.

### Primary endpoint

Analysis of reliability between HR measured by the gold standard (ECG via Mindray ePM10) and HR measured by rPPG (using the Caducy application) following a 30-s recording period. Up to two measurement attempts will be permitted for each method. If a successful measurement is not achieved within two attempts for either method, the primary endpoint will be considered unevaluable for that participant.

### Secondary endpoints

Reliability between gold standard (ECG) HR measurements and rPPG HR measurements using a recording period of 60 s.Reliability between gold standard (impedance RR measure via Mindray ePM10) RR measurements and rPPG RR measurements using a recording period of 60 s.Reliability between gold standard RR measurements and rPPG RR measurements using a recording period of 30 s.Reliability of HR measurements between the Mindray ePM10 and rPPG over 30 s, stratified by age group (3 years to 7 years, 7 years to 12 years and 12 years to 18 years) and by Fitzpatrick skin phototype classification.Reliability of RR measurements between the Mindray ePM10 and rPPG over 30 s, stratified by age group (3 years to 7 years, 7 years to 12 years and 12 years to 18 years) and by Fitzpatrick skin phototype classification.Parental satisfaction with the use of the Caducy application, assessed using a 5-point Likert scale (1=‘Not at all useful’ to 5=‘Extremely useful’).Participant satisfaction (children/adolescents aged 3–17 years) with the use of the Caducy application, assessed using a 5-point Likert scale (1=‘Not at all useful’ to 5=‘Extremely useful’).Rate of measurement failure for each technique (rPPG and thoracic electrodes), defined as the inability to obtain a valid measurement value or the presence of clearly erroneous measurements attributable to poor signal quality or acquisition failure.

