### Statistical analysis

Analyses will be performed by a biostatistician from the Department of Clinical Research at the CHU of Nice. The assumptions underlying each statistical test will be verified prior to analysis. Results will be considered statistically significant at the 5% level (p<0.05), unless specified otherwise. Analyses will be conducted using SAS Enterprise Guide V.7.1 (SAS Institute Inc., Cary, NC, USA). Descriptive statistics will be calculated for the study population and key study parameters. Categorical variables will be presented as absolute and relative frequencies, with 95% CIs where appropriate. Quantitative variables will be presented using means, SD, medians and IQRs. A flowchart illustrating participant flow (including numbers included and followed up) will be provided. Reliability will be assessed using the intraclass correlation coefficient (ICC) with a 95% CI to measure the agreement between the two measurement systems. Missing data will not be imputed.

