### Sample size

We hypothesise an ICC of 0.90. To estimate this ICC with a precision of ±2% and considering a type I error of 5% and a type II error of 10%, the required sample size is 430 participants.^12^ To account for potential technical issues (10%), to facilitate subgroup analyses and considering our active patient pool, the total targeted sample size in this study will be 600 participants.

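### Age-band ICCs mix device error with the spread of rates between children, so as the only stated agreement measure they cannot show whether rPPG accuracy differs by age

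*Protocol article*

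**What the plan says.** The Secondary endpoints section of the protocol article lists "Reliability of HR measurements between the Mindray ePM10 and rPPG over 30 s, stratified by age group" and, in parallel, "Reliability of RR measurements between the Mindray ePM10 and rPPG over 30 s, stratified by age group". The strata are given as "3 years to 7 years, 7 years to 12 years and 12 years to 18 years) and by Fitzpatrick skin phototype classification". Under Study procedure, phototype is recorded as "phototype according to Fitzpatrick’s classification ranging from phototype 1 to 6". The Eligibility criteria admit "Age 3 to 17 years", so each age band covers only part of the sample's age range.

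The Statistical analysis section names one agreement statistic for all reliability endpoints: "Reliability will be assessed using the intraclass correlation coefficient (ICC) with a 95% CI to measure the agreement between the two measurement systems". It states no bias, limits of agreement or other error measure in beats or breaths per minute.

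The Sample size section says "We hypothesise an ICC of 0.90". This is a single value for the whole sample, and the section gives subgroup analyses as one reason for enrolling 600 rather than 430. No heart-rate or respiratory-rate variance, no threshold per stratum and no test between strata is stated.

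**The concern.** The ICC is the between-child variance divided by the sum of between-child variance and error variance. It answers how well the measurement separates the children in a given group. It does not say how many beats or breaths per minute the device is off.

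Resting rates can be expected to change with age between 3 and 17 years. Splitting by age then removes some of the between-child variance and leaves device error as it was. Bands may also differ in their own spread. Two things follow:

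- A band can show a lower ICC than the whole sample, or than another band, with no difference in device error.
- A band with wide spread can show a reassuring ICC although the device is less accurate there.

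The study's aim includes accuracy in paediatric patients, and a reader will look to the age-band results to see whether the device is equally accurate in the youngest. The subgroups are also part of the case for the sample size. Allowing 10% for technical issues takes 430 to 430/0.9 ≈ 478, and the remaining 122 or so children are justified by subgroup analyses and the available patient pool.

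**Working it through.** **The plan's own figure.** Inputs from the Sample size section: ICC 0.90, precision ±0.02, type I error 5%, type II error 10%, two methods. For two methods the asymptotic standard error of the ICC is (1 − r²)/√N. Requiring a 95% CI half-width of 0.02 with 90% assurance means solving

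[1.96 × 0.19 + 1.2816 × (1.96 × 2 × 0.90) × 0.19/√N] / √N = 0.02.

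This gives N = 428.3, rounded up to 429, against the stated 430. The figure reproduces, and it refers to the whole sample.

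**Effect of splitting by age.** Set total variance to 1, so that a pooled ICC of 0.90 means true between-child variance 0.90 and error variance 0.10. Let f be the share of true variance that lies between age bands. With device error unchanged, the average within-band ICC is

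0.9(1 − f) / [0.9(1 − f) + 0.1].

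The protocol gives no figure from which f could be derived, so f is an assumption and a range is shown.

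| f (assumed) | Within-band ICC | Fall from 0.90 |
|---|---|---|
| 10% | 0.81/0.91 = 0.890 | 0.010 |
| 20% | 0.72/0.82 = 0.878 | 0.022 |
| 30% | 0.63/0.73 = 0.863 | 0.037 |
| 50% | 0.45/0.55 = 0.818 | 0.082 |

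**Yardstick.** The ±0.02 is not the precision within a band. With 600 × 0.9 = 540 evaluable children in equal thirds (assumed), each band has 180. The half-width is 1.96 × (1 − r²)/√(n − 1):

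- ICC 0.90: 1.96 × 0.19/√179 = 0.028
- ICC 0.863: 1.96 × 0.2552/√179 = 0.037

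The shift is therefore within sampling error at f = 10% or 20%, about one half-width at 30%, and clearly larger at 50%.

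**Simulation check.** Assumptions: 540 children, band means 12.5 bpm apart, within-band SD 15 bpm (f = 32%), equal error throughout, 2000 runs. The pooled ICC was 0.900 and each age band about 0.859. Six phototype strata unrelated to heart rate gave about 0.898 each, so there was no real drop.

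**Unequal spread between bands.** Keep means 12.5 bpm apart and assume band SDs of 20, 15 and 12 bpm.

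- Mean within-band variance: (400 + 225 + 144)/3 = 256.3
- Between-band variance: (12.5² + 0 + 12.5²)/3 = 104.2
- Error variance for a pooled ICC of 0.90: (256.3 + 104.2)/9 = 40.06
- Band ICCs: 400/440.06 = 0.909; 225/265.06 = 0.849; 144/184.06 = 0.782

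Device error is the same in all three bands. The SD of the differences is √(2 × 40.06) = 8.95 bpm in each, so the limits of agreement are bias ± 1.96 × 8.95 = ± 17.5 bpm in each.

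**Masking.** Raise the error SD in the band with SD 20 by a factor of 20/15. Its error variance becomes 40.06 × (20/15)² = 71.2 and its ICC 400/471.2 = 0.849, the same as the band with SD 15. Its limits of agreement widen to ± 1.96 × √(2 × 71.2) = ± 23.4 bpm. The ICCs are equal although the error SD is one third larger.

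**The case against.** The strongest reply is that the protocol lists reliability by stratum and nothing more. It states no test between strata, no ranking and no threshold per stratum. A band's ICC is a valid description of reliability in that band, and the error arises only if a reader takes it for device error. The endpoints are secondary, and further agreement measures are often left to the statistical analysis plan. Most of this stands, and it limits the severity. It does not remove the point, because the protocol fixes both the statistic and the strata, and that statistic does not answer the accuracy question the strata invite.

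Three stronger readings are tempting and are not supported.

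- A reader might infer that the age bands will wrongly look worse. The size depends on a variance share the protocol does not give, the fall is only 0.01 to 0.02 at 10% to 20%, and a band with wide spread can exceed the pooled value (0.909 against 0.90 above).
- A reader might extend the argument to phototype. Phototype strata do not narrow the age range, and nothing in the protocol links phototype to age or to the spread of either rate.
- A reader might set the falls against the planned ±0.02. That is whole-sample precision; a band has about ±0.028 at ICC 0.90, and more at lower ICCs.

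**Conclusion.** The point holds for the age-stratified endpoints, for both heart rate and respiratory rate at 30 s. Age-band ICCs cannot be compared with each other or with the pooled value as a measure of device accuracy, and no other agreement measure is stated.

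With error fixed at a pooled ICC of 0.90, the average within-band value runs from 0.89 to 0.82 as the assumed share of variance between bands runs from 10% to 50%. Individual bands can lie on either side of the pooled value. All of this rests on assumed variances and on equal device error across bands. For phototype the point is conditional: it applies only if spread or age mix differs between classes.

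The consequence is a risk of misreading secondary results in either direction. The primary analysis and the sample size of 430 stand. The change is worth making but does not affect the validity of the main result.

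**What to change.** For each age band and phototype stratum, make bias and limits of agreement the measure by which device accuracy is judged, in beats per minute for heart rate and breaths per minute for respiratory rate, with confidence intervals. Keep the ICC with its 95% CI as a supplement, print the stratum's between-child SD beside it, and state that ICCs are not compared across strata. A model of the paired differences on age band and phototype is an optional addition.

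This needs a few lines in the analysis plan before the database is locked and a small amount of extra analysis. It uses the paired readings already collected and needs no further children or procedures.

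### Stratified ICCs are the only stated analysis of the age and phototype endpoints, and they do not estimate how device error changes with skin type or age

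*Protocol article*

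**What the plan says.** All places are in the protocol article.

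- **Secondary endpoints:** one endpoint is "Reliability of HR measurements between the Mindray ePM10 and rPPG over 30 s, stratified by age group", with bands of 3 to 7, 7 to 12 and 12 to 18 years. The list of strata ends "12 years to 18 years) and by Fitzpatrick skin phototype classification". A parallel endpoint covers RR at 30 s.
- **Statistical analysis:** one method is given for every reliability endpoint: "Reliability will be assessed using the intraclass correlation coefficient (ICC) with a 95% CI". A general 5% significance level is stated but not attached to any comparison between strata.
- **Study procedure:** "The following data will then be collected: sex, age and phototype", the last graded 1 to 6 on Fitzpatrick's scale.
- **Sample size:** 430 children are needed for the main ICC. The target of 600 allows for 10% technical problems and is also meant "to facilitate subgroup analyses".

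The article gives no between-stratum difference, no trend and no joint age-and-phototype estimate. It also does not say that strata will be compared, by what rule, or whether the age and phototype strata are crossed.

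**The concern.** Skin type is a natural question for this device: the Medical device section says that HR is derived from colour-channel variation in facial skin, and the article lists the range of ages and phototypes as a strength. A reader shown up to six phototype ICCs will compare them. The planned output supports that comparison poorly, for two reasons.

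- A stratum ICC depends on the spread of true HR or RR in that stratum as well as on device error, so it is a blunt measure of a change in error.
- Phototype is ordered and age is continuous. Separate strata use neither fact and leave some classes with few children.

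At stake is a report in which similar-looking ICCs with wide intervals are read as showing that the device works equally well across skin types. The Discussion envisages use by parents, in teleconsultation and by emergency services.

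**Working it through.** **1. The plan's own figure.** The Sample size section gives "We hypothesise an ICC of 0.90", "To estimate this ICC with a precision of ±2" (per cent), and "considering a type I error of 5% and a type II error of 10" (per cent). Read these as a 95% CI half-width of 0.02 with 90% assurance, for two measurements per child. With f = (1 − 0.90)(1 + 0.90) = 0.19 and slope |f′| = 2 × 0.90 = 1.8, the half-width at n is

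1.96 × [f + 1.2816 × 1.8 × f/√(n − 1)] / √(n − 1).

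At n = 430, √429 = 20.71 and f/20.71 = 0.00917. The half-width is 1.96 × (0.19 + 0.0212)/20.71 = 0.01998, which meets 0.02. So 430 reproduces, and the sample size is not at fault here.

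**2. What is left per phototype.** Evaluable children: 600 × 0.9 = 540. The article gives no phototype mix, so two cases are assumed. For an ICC of 0.90, the F-based 95% CI is:

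- equal classes, 540/6 = 90 children: 0.852 to 0.933;
- a class holding 3%, about 16 children: 0.744 to 0.964.

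**3. Power to show a steady loss of accuracy.** Assumptions, none of them in the article: HR falls 3 bpm per year of age with residual SD 13 bpm; rPPG error SD is 6 bpm in type I and rises by a fixed percentage per type (10% gives 6 × 1.1⁵ = 9.7 bpm in type VI; 8% gives 6 × 1.08⁵ = 8.8 bpm). Three ways of looking for the change were compared: any two stratum ICC intervals failing to overlap; any two stratum SD-of-difference intervals failing to overlap; and an age-adjusted linear trend of the absolute difference at the 5% level.

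| Rise per type | Stratum ICCs | Stratum SDs | Adjusted trend |
|---|---|---|---|
| 8% | 31–43% | 63–83% | 77–94% |
| 10% | 43–63% | 83–94% | 93–99% |

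Ranges are over the assumed mixes. With no true effect, the ICC comparison and the trend each signal in about 5%. A second set of runs, with type VI at 3/5/10% of children, gave for the 10% rise 38/43/64%, 78/88/95% and 89/95/99%, and for the 8% rise 24/32/43%, 60/68/82% and 74/82/94%. The SD comparison was slightly liberal there (7–8% under no effect).

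**4. Where the gain comes from.** In the second set at 10%, moving from ICC to SD adds 78 − 38 = 40, 88 − 43 = 45 and 95 − 64 = 31 points. Moving from SD strata to the ordered trend adds 11, 7 and 4. At 8% the second step adds 14, 14 and 12. In the tabulated runs the second step is worth about 5 to 18 points. Age adjustment itself added no power.

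**5. Keeping the ICC throughout.** For a linear fall in ICC across types, a 5-df comparison of classes against a 1-df trend gives, over a light-heavy and a uniform mix: 0.92 to 0.88, 11–20% against 19–38%; 0.92 to 0.84, 26–58% against 48–82%; 0.92 to 0.80, 49–85% against 75–97%. The trend is better each time, but it too usually misses the smallest fall.

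**6. Confounding by age.** Let error depend only on age (SD 9 bpm at 3 years, 3.75 at 18). Some pair of phototype ICC intervals fails to overlap in 9% of trials at zero age–phototype correlation, and in about 10%, 13% and 19% at correlations of 0.1, 0.2 and 0.3. An age-adjusted phototype trend stays at 4–6%.

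**7. Where a linear trend is worse.** If error rises only in types V and VI, the linear trend detects it in 62% of trials and separate stratum SDs in 75%.

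**The case against.** The strongest reply is that the article plans estimation within strata and nothing more. How well the device agrees in children of type V is a legitimate question, and a stratum ICC answers it directly. No rule about overlapping intervals is stated and no age or skin effect is to be declared. A model for secondary subgroup endpoints is often left to a full protocol or analysis plan, neither of which is shown. All this stands: the text contains no wrong figure or contradiction on this point, and the overlap rule used above is only a yardstick for what a reader of the tables could see.

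It does not dispose of the point. Stratified ICCs are a definite stated choice for named endpoints that partly justify the move to 600, and a better-directed analysis is available on the same data. Crossing the strata would not help: 3 × 6 = 18 cells average 540/18 = 30 children, still with no trend estimate.

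Two stronger readings are tempting and are not supported.

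- **That an age effect will pass for a skin effect.** This needs age and phototype to be associated, which the article does not state. An unadjusted phototype trend would be falsely significant in 8%, 24% or 48% of trials at correlations of 0.1, 0.2 or 0.3, but no such trend is planned. For the planned strata the excess over the 9% baseline is about 1, 4 and 10 points.
- **That the whole power gap is due to ignoring the phototype order.** Most of it comes from using the ICC rather than the paired difference.

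**Conclusion.** The point holds as an improvable analysis choice for secondary endpoints; the primary endpoint is untouched. As stated, the plan yields agreement within strata and no estimate of how error changes per phototype step or per year of age. For an HR error SD rising 8 to 10% per type, with 540 evaluable children, comparing stratum ICC intervals would reveal the change in about 31 to 63% of trials, against 77 to 99% for the adjusted trend. These figures rest on assumed phototype mixes, error sizes and HR spread. A smaller gradient would often be missed by either approach. The gain was simulated for HR only; RR is read from upper-chest movement, so it should not be assumed to be the same there. Age adjustment is a safeguard in case age and phototype prove to be associated, not a correction of a demonstrated bias.

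**What to change.** Keep the ICC tables by age band and phototype as description. Add to the Statistical analysis section, for HR at 30 s and likewise for RR at 30 s:

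- a regression of the paired difference (rPPG minus monitor), and one of its absolute value, on phototype (ordered, 1 to 6) and age (continuous), in all evaluable children, with robust standard errors;
- the change per phototype step and per year of age, each with a 95% CI;
- a check for non-linear loss, with phototype as categories or types V and VI against the rest;
- a sentence saying that any statement that accuracy does or does not vary with skin type or age rests on these estimates, not on comparing stratum ICCs.

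The cost is a few lines of text before the database is locked and one more table. No extra children, measurements or procedures are needed, because age and phototype are already collected. The drawback is the assumption of a roughly monotone trend across phototypes, which the categorical check is there to test.
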